**Research Proposal**

---

MRSE, 30 without MRSE) for muscle strength and fatigability testing, and 30 of them will also be investigated by muscle biopsies (see figure 1 and table 1 for details).

**Functional assessment and blood samples**

A case-control approach will be used to compare patients under statin treatment with and without MRSE. After initial testing while under statin treatment, statin treatment will be stopped for 2 months followed by retesting. Recent studies have shown that most statin MRSE as well as structural muscle damage appearance/disappearance occurs within a two month period of statin introduction/withdrawal [1, 13]. A control group of 10 statin-naïve patients will also be included for test-retest variability assessment of all parameters.

Following screening, 60 patients presenting MRSE (assessed by a standardized questionnaire; see **Appendix 3, questionnaire 3**) under statin monotherapy (any statin, any dosage) as well as 30 patients without MRSE under statin monotherapy (paired for statin and dosage with the MRSE cohort) will be evaluated. Muscle strength and fatigability will be tested by standardized procedures before and after two months of stopping statin monotherapy. Briefly, strength of the extensors and flexors muscles of the dominant leg will be quantified with a Biodex isokinetic dynamometer available in our research centre. Forces will be tested during 3 reps at 60 and 180 deg/sec and endurance during a 15 reps test at 180 deg/sec. These tests will be preceded by a 5 reps warm-up at 60 deg/sec including one movement at maximal voluntary contraction [46]. Each maximal concentric contraction will be performed in the first 90 degrees of the knee range of motion. Patients will sit in an upright position and mechanical axis and resistance pads will be aligned according to the manufacturer's guidelines. The results will be reported in Newton-meters (Nm). Peak torque, rate of torque development and total work values will be obtained following these isometric and isokinetic measurements. These groups of muscles were selected because muscle weakness or myalgias with statins are most frequently localized in lower limbs. Handgrip strength of the dominant hand will also be tested in a static mode with a Jamar dynamometer (best of 3 repetitions). These testing procedures are well standardized, easy to perform and very reproducible, and are routinely used in the department of physical therapy at our centre. Test-retest variability for the Biodex measurements is shown to be within  $\pm 15\%$  [46], which our personal experience confirms. The primary efficacy parameter will be the percent change for these measurements from baseline to end of each phase of the study.

Before each muscle function test, venous punctures will also be collected to assess muscle and liver enzyme contents as well as 25(OH)D concentration in serum (DiaSorin RIA). These serum assays are routinely performed at the clinic and research center of CHUL. The percent change in serum CK, ALT, AST and creatinine from baseline to end of each phase of study will be evaluated for each patient. The vitamin D status of patients will be assessed using serum 25(OH)D levels. Plasma (or serum) 25(OH)D concentration is generally considered to be the best metabolite to reflect vitamin D status [47]. Patients with abnormal clinical results will receive standard medical care for their condition.

**Preliminary data.** To demonstrate the feasibility of our approach for evaluating functional changes upon drug withdrawal in patients suffering from statin-related MRSE, preliminary data have been gathered on muscle strength and endurance in 9 patients and are presented in **APPENDIX 1**. Part of this preliminary data has been presented in abstract form [48].

Six men and 3 women ( $57 \pm 9$  years) with MRSE that could affect their compliance to statins were subjected to a preliminary assessment of the functional capacity of knee flexor and extensor muscles when taking statins, and to a second evaluation 2 to 3 months after drug cessation. The strength of extensors and flexors was measured in a sitting position on a Biodex isokinetic dynamometer after 3 maximal contractions at 60 degrees per second. Power, endurance and fatigability were measured after 15 repetitions at 180 degrees/second. Muscle symptoms while taking statins and after cessation were documented as well as blood CK and AST levels.

---

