**Research Proposal****Muscle-Related Side Effects of Statins: Functional Impact, Mechanisms, and Potential Reversibility with Vitamin D Supplementation****1.0 PROJECT OVERVIEW**

Amongst the most prescribed drugs worldwide, statins play a key role in health care by improving the cardiovascular outcomes of many patients. However, the use of statins is not without side effects. Besides the rare cases of rhabdomyolysis, other skeletal muscle-related side effects (MRSE) such as myalgia, cramps, and fatigue are estimated to affect 10% or more of the patient population under statin treatment [1]. Because approximately 10% of the population is taking statins on a daily basis [2], we can then extrapolate that over 300,000 Canadian patients are suffering from MRSE. Surprisingly little is known about the functional impact of these symptoms or the mechanisms responsible for their appearance. More importantly, health care professionals do not know how to deal with or relieve patients from MRSE. This unique project fills in this knowledge gap by combining functional, histological, and molecular approaches to improve our understanding of skeletal muscle-statin interactions and by testing an alternative treatment to reduce MRSE.

**Objectives:** The two main objectives of this study are the following:

- 1) To test muscle strength and fatigability and investigate skeletal muscles at the histological and molecular levels in statin treated patients with and without MRSE; and*
- 2) To assess the usefulness of vitamin D supplementation in improving muscle function and structure and reducing muscle-related side effects.*

More specifically, this project will enable us to determine (1) whether a loss of muscle strength and endurance can result from statin treatment, (2) whether statin therapy influences muscle morphology (in particular mitochondrial content and function) and increases muscle fiber degeneration in some susceptible subjects in relation to functional changes, and (3) if vitamin D supplementation can decrease statin-induced MRSE and muscle tissue damage while preserving muscle function and the cardiovascular benefits (decreased low-density lipoprotein cholesterol levels) of the drug.

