**Research Proposal**

---

Subjects (see **APPENDIX 1, Table 1**) in our study were statin users and had muscle side effects (cramps, myalgia, reduced muscle endurance) evaluated with our in-house questionnaire (see **APPENDIX 3, questionnaire 3**). All subjects were in primary cardiovascular prevention. Different statins were used by different participants, the majority at low doses (the highest being 20 mg).

After statin withdrawal, all subjects reported important decreases in the level of pain experienced (**APPENDIX 1, Figure 1**), and 70% showed functional improvements in at least one Biodex measure of muscle performance (**APPENDIX 1, Figure 2**). On average, the strength of the extensor and flexor muscles increased by  $22\pm 43\%$  and  $17\pm 28\%$  respectively, power by  $28\pm 64\%$  and  $29\pm 41\%$ , and endurance by  $28\pm 57\%$  and  $20\pm 35\%$  (means $\pm$ SD). No effects were observed on blood CK and AST values (**APPENDIX 1, Table 2**).

Our preliminary results show that cessation of statin therapy increased muscle functional capacity in the majority of subjects who experienced *a priori* muscle discomfort. ***Since this condition could affect the pharmacological compliance and potentially modify the cardiovascular benefits of statins, it is imperative to better characterize this dysfunction and develop approaches to reduce its impact.***

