### **Histological assessment of skeletal muscle**

For a subset of 30 of the patients in the study (20 presenting MRSE and 10 without MRSE), percutaneous needle biopsies of the *vastus lateralis* muscle will be performed, before and after two months of discontinuation of statin monotherapy, in our outpatient surgical center. [name] (Laval University), who has performed this procedure literally hundreds of times over the years, will be responsible for biopsies (see **letter of collaboration**). This technique is relatively painless (especially in patients with normal CK), well tolerated, can be performed within 20 minutes, and is routinely used in our laboratory for repeated measures over time [49]. A control group of 10 statin-naïve patients will have the same muscle functional testing and venous punctures collection at the start of the study and two months later; 5 of these will also have muscle biopsies.

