## **5.0 STATISTICAL ANALYSES**

Although there are no published data on the loss of muscle force in humans following statin treatment, experiments using men with coronary artery disease showed that  $n = 10$  to  $20$  is sufficient to distinguish differences between groups [58]. Based on the high accuracy of the Biodex apparatus and our preliminary data, we calculate that a total of 60 MRSE suffering patients will be sufficient to demonstrate effects on muscle function by statin withdrawal or vitamin D supplementation (30 per group, one with vitamin D, the other with placebo - see APPENDIX 3 for Power Calculations). These sample sizes are similar to those producing data showing reversible myositis-myalgia in statin-treated low serum 25(OH)D patients receiving vitamin D repletion [43, 44]. For biopsies, the number of subjects in each study group was determined based on our previous work (*e.g.*, [49]), biopsy feasibility and the availability of patients from our clinic [59]. From the patient case reports documented with some of these MRSE and considering the analytical precision of the methods proposed, we are confident that we will show statistically significant differences between MRSE suffering and not suffering patients [13].

Statistical analyses will test the comparison of subgroups (with/without symptoms and with/without vitamin D repletion) on the percent change from baseline (end – baseline) of specific measurements. Changes from baseline (end – baseline) of all clinical muscle symptoms will be also analyzed. Normal distribution of fasting marker levels will be examined and, if necessary, they will be normalized by transformation prior to statistical analyses in order to reduce the skewness of their distribution. One-way ANOVA will be used to compare means of continuous variables. Differences in proportions (*e.g.* proportion of patients having increments in one or more specific markers) will be compared using either the Chi-square test, or the Fisher's exact test when appropriate. Statistical analyses will be performed using SAS (SAS Institute Inc.) and/or JMP (SAS Institute Inc.) software. All tests will be two-tailed and considered statistically significant when alpha level  $< 0.05$ .

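### The effect of stopping statins on muscle function has no stated comparison that separates it from practice, because the statin-naive controls are used only for test-retest variability

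*Protocol*

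**What the plan says.** Section 1.0 of the protocol sets the question. Specific aim (1) asks "whether a loss of muscle strength and endurance can result from statin treatment", and Hypothesis 2 predicts that muscle function in MRSE patients improves once the statin is stopped. Section 5.0 adds that 60 MRSE patients are enough to show effects of statin withdrawal or of vitamin D.

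Section 3.0, Objective #1 fixes the order of testing: "After initial testing while under statin treatment, statin treatment will be stopped for 2 months followed by retesting". This applies to the 60 patients with MRSE and to the 30 without, who are paired with them for statin and dosage. The endpoint is a within-patient change: "The primary efficacy parameter will be the percent change for these measurements from baseline to end of each phase of the study".

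The role given to the 10 statin-naive patients is: "A control group of 10 statin-naïve patients will also be included for test-retest variability assessment of all parameters". The subsection on histological assessment says that they "will have the same muscle functional testing and venous punctures collection at the start of the study and two months later".

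Section 5.0 then names the comparisons: "Statistical analyses will test the comparison of subgroups (with/without symptoms and with/without vitamin D repletion) on the percent change from baseline". The statin-naive group is not among them.

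**The concern.** The question is about the effect of stopping the drug, but neither named comparison estimates it. In the with/without-symptoms contrast both groups stop their statin, so it measures how much more the MRSE patients change. If statins weakened both groups equally, it would show nothing. The change within the MRSE group is closer to Hypothesis 2. However, the off-statin test is always the second maximal-effort test, so any gain from having done the test before is added to any recovery. The only familiarisation described is a short warm-up in the same session.

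The preliminary data show how such a result would be read. Nine patients were tested on and then off statin without controls, and the protocol concludes: "Our preliminary results show that cessation of statin therapy increased muscle functional capacity in the majority of subjects". A positive change in the main study could be read the same way, although a group tested over the same interval without a statin change will be available.

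**Working it through.** **Inputs from the protocol**
- 60 MRSE patients, 30 without MRSE, 10 statin-naive controls; two-sided alpha 0.05.
- Pilot percent changes in strength (n = 9, mean ± SD): extensors 22 ± 43, flexors 17 ± 28.
- Biodex test-retest variability within ±15%. This is a spread; no mean shift between first and second test is given.

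**Assumptions**
- Practice gain g of 3, 5 or 10 points.
- SD of change in controls: 15% (reading ±15% as an SD) up to the MRSE value.

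**The plan's own figure.** The 60 (30 per arm) cannot be reproduced, because the target power and design effect are in an appendix that is not shown. With extensor values and an assumed 80% power, a single-group before-after test needs (43 × (1.96 + 0.84) / 22)² ≈ 30 patients, and a two-group comparison needs 60 per group. Neither match shows which method was used.

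**What each contrast estimates.** Write W for the withdrawal effect and g for the practice gain.
- Change within MRSE patients: W(MRSE) + g.
- MRSE minus non-MRSE: W(MRSE) − W(non-MRSE), if g is equal in both. Pain at the first test could make it unequal.
- MRSE minus statin-naive: W(MRSE), if g is equal in both.
- Vitamin D minus placebo (randomised): a common g cancels.

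**Uncorrected before-after test, n = 60, W = 0.** Noncentrality = g / (SD / √60); two-sided rejection rate from the noncentral t with 59 df.

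| Assumed g | SD 43 | SD 28 |
|---|---|---|
| 3 points | 8% | 13% |
| 5 points | 14% | 28% |
| 10 points | 43% | 78% |

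With g = 0 the rate is 5%.

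**Precision of the corrected estimate (95% half-widths).**
- MRSE alone, SD 43: 1.96 × 43 / √60 = 10.9 points.
- Minus controls, control SD 15: 1.96 × √(43²/60 + 15²/10) = 14.3.
- Minus controls, control SD 43: 1.96 × √(43²/60 + 43²/10) = 28.8.
- MRSE SD 28: 11.7 (control SD 15) or 18.7 (control SD 28).

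With equal SDs, a 60 versus 10 comparison has about 32% power for 22 ± 43 and 42% for 17 ± 28. The uncorrected test in 60 has about 97% and over 99%, but for W + g.

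**Pilot.** Extensors: SE = 43/√9 = 14.3, t = 1.53, p = 0.16, 95% CI −11 to 55. Flexors: SE = 28/√9 = 9.3, t = 1.82, p = 0.11, 95% CI −5 to 39. Apart from the lack of controls, these strength results are imprecise.

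**The case against.** The best reply is that the protocol does plan a concurrent comparison. Patients without MRSE follow the same order over the same interval, and section 5.0 compares the two groups on change. A common practice gain cancels there, and that contrast bears on the Objective #1 outcome of reduced function in patients with myalgia. This stands. A reader might infer that practice gains will count as recovery throughout the trial. The documents do not support that, and the randomised vitamin D comparison is not affected by a common gain either.

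Second, section 5.0 names one-way ANOVA and tests of proportions, not a paired test in MRSE patients, and the practice gain is assumed. This also stands. The rejection rates describe what happens if the within-group change is tested and read as Hypothesis 2 invites; they are not error rates of a specified analysis.

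Third, a test-retest assessment could include the mean shift, ANOVA could take a third group, and an analysis plan that is not shown might settle the matter. This stands only in part. The protocol itself gives the controls their role, lists the comparisons and states the causal hypothesis, and these do not fit together.

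Fourth, subtracting the controls' change does not remove expectancy. No masking of withdrawal is described, and the controls stop nothing. This stands and limits what the correction can claim.

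**Conclusion.** The point holds in a limited form. The protocol asks about the effect of stopping statins but names no comparison that isolates it from practice, although the controls needed for one are already scheduled. The MRSE versus non-MRSE contrast is sound for the excess change in MRSE patients and for nothing wider.

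The size is conditional, since the practice gain may be small and the SDs come from nine patients. Even an assumed gain of 3 points would raise the rate of significant uncorrected results above the nominal 5%. It would be wrong to infer that the documents show a practice gain, that the pilot improvement is an artefact, or that aim (1) cannot be addressed at all. They show only that an uncorrected gain cannot be attributed to stopping the statin.

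**What to change.** State in section 5.0 that the withdrawal effect on strength and endurance is the two-month change in statin users, with MRSE and non-MRSE patients taken separately, minus the two-month change in the statin-naive controls, reported with its 95% confidence interval. Add that if this interval is too wide to be informative, the conclusion is limited to the MRSE versus non-MRSE difference and the uncorrected gain is not attributed to statin cessation.

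The on-off-on sequence in the 30 MRSE patients on placebo can serve as supporting evidence: a statin effect should reverse on rechallenge, while a practice gain should not. It separates the effect from practice only, because expectancy could also reverse on rechallenge. Rechallenge length varies too, as patients may stop early. The report should name expectancy as a remaining limitation.

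No new patients or visits are needed. The cost is precision: subtracting the change in only 10 controls widens the interval as shown in the working. If the control SD is near the MRSE value, the interval could not exclude zero at the pilot's 22%.

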**Hypotheses:** 1) Patients under statin monotherapy and suffering from statin-induced MRSE show reduced muscle strength and increased fatigability associated with an increased prevalence of cell damage, proteolytic markers, and perturbed mitochondria. 2) The cessation of statin monotherapy improves muscle function and reduces biological markers of muscle cell degeneration in patients with MRSE. 3) Vitamin D supplementation followed by statin reintroduction protects against statin-induced MRSE.

**Patient population:** Men and women aged between 30-60 years (inclusive) and affiliated with the cardiovascular prevention lipid clinic at the Laval University Hospital Research Centre (CHUL) will be included in this study. Patients treated with statin therapy for the first time in the last year with or without MRSE and with normal creatine kinase (CK) blood levels will be recruited. These patients must not have taken statins or lipid-lowering drugs before the last year or consume vitamin D supplements. MRSE must clearly have begun after statin introduction. These patients will be in low cardiovascular risk primary prevention, allowing us to modify their lipid-lowering drug regimen for a short period of time.

**Impact:** A better understanding of the cellular and molecular events leading to muscle pain, damage and dysfunction in the presence of statins is essential for the design of effective therapeutic modalities. We are convinced that this project will provide the basic foundation for this and may position Canada as a world leader on how to deal with MRSE associated with statins. Lastly, the present proposal also proposes an alternative treatment by testing the combination of statins and vitamin D supplementation to alleviate MRSE, an area in which clinical research and transferable solutions to patients are crucially needed.

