**Statin-induced myopathy.** Statins are generally well tolerated and very serious side effects appear to be rare [4]. The one notable serious adverse reaction to statin therapy is *rhabdomyolysis* (muscle symptoms with marked creatine kinase elevation and creatinine elevation [4]), which was observed early on with lovastatin in cardiac transplant patients [5]. In the worst cases, severe myoglobinuria accompanied by serum CK levels greater than 10 times normal, acute renal failure and even death can occur. Only a small fraction of patients who are treated with statins will develop such a severe myopathy (perhaps 1 in 10,000 patients) [6]. Based on FDA reports, the rate of fatal rhabdomyolysis was 16- to 80-fold greater for cerivastatin as compared to other statins, particularly at higher doses, but the mechanisms leading to such muscle toxicity are still poorly understood. In clinical practice, some non-specific predisposing factors have been pointed out and included advanced age, low body weight, female gender, use of multiple medications, multi-systemic disease, acute illnesses and major surgery [4]. Information on these issues as well as on the confusing area of low-grade myopathy (with normal CK) associated with statin use remains, however, extremely limited.

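### The on-statin comparison of muscle strength between patients with and without MRSE is paired on drug and dose only and has no stated adjustment for sex, age or body weight, so an imbalance in these can bias it

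*Protocol*

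**What the plan says.** - **The claim about level.** Hypothesis 1 (1.0 Project Overview) reads: "Patients under statin monotherapy and suffering from statin-induced MRSE show reduced muscle strength and increased fatigability". Withdrawal is the subject of a separate Hypothesis 2. Primary outcome (2) of Objective #1 is likewise to demonstrate reduced strength and endurance in patients with statin-related myalgia.
- **The design.** Objective #1, Functional assessment and blood samples: "A case-control approach will be used to compare patients under statin treatment with and without MRSE".
- **The comparators.** Same section: "30 patients without MRSE under statin monotherapy (paired for statin and dosage with the MRSE cohort) will be evaluated", against 60 patients with MRSE. No other pairing factor is given. Age and sex appear only as stratification factors for the vitamin D randomisation in Objective #2.
- **The unit.** Biodex results are reported in Nm, with no scaling to body size.
- **The test.** Section 5.0: "One-way ANOVA will be used to compare means of continuous variables". No covariates are named.
- **The main scale.** "The primary efficacy parameter will be the percent change for these measurements from baseline to end of each phase of the study". Section 5.0 compares subgroups ("with/without symptoms and with/without vitamin D repletion) on the percent change from baseline (end – baseline) of specific measurements".
- **Risk factors.** The background on statin-induced myopathy says that "some non-specific predisposing factors have been pointed out and included advanced age, low body weight, female gender". It adds that information on low-grade myopathy with normal CK is very limited.

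**The concern.** Both sexes aged 30 to 60 are eligible. Women, older people and lighter people on average produce less torque in Nm. The protocol names the same three features as predisposing to statin myopathy. If they are more common in the MRSE group, that group will look weaker even if statins have done nothing to its muscles, and the error favours Hypothesis 1. If they are less common, a real deficit is masked. Pairing on statin and dose does nothing about this. The Objective #2 stratification balances vitamin D against placebo, not MRSE against non-MRSE.

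The protocol accepts this kind of argument: its background section treats the wide age range of an earlier biopsy study as a potential confounder, because strength loss accelerates at around 60.

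At stake is a named primary outcome of Objective #1. The report could attribute to MRSE a difference that comes from case mix, or miss a true one because variation between the sexes is left in the error term.

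**Working it through.** **The plan's own figure.** Section 5.0 gives 60 MRSE patients (30 per randomised arm) and refers to an appendix that is not shown. It gives no figure for MRSE against non-MRSE, so there is nothing to reproduce.

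**Inputs from the protocol.** 60 MRSE and 30 non-MRSE patients; two-sided alpha 0.05.

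**Assumptions, not in the protocol.** Men's mean torque = 1; women's mean k = 0.6 to 0.7; within-sex CV 20%; no true MRSE effect; fraction of women p = 0.60 in MRSE and 0.40 in non-MRSE.

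**Formulas.**
- Group mean: m = p·k + (1 − p).
- Within-sex variance: p·(0.2k)² + (1 − p)·0.2². Between-sex variance: p(1 − p)(1 − k)².
- SE = pooled SD × √(1/60 + 1/30) = pooled SD × 0.2236.
- Chance of p < 0.05 from the non-central t with 88 df.

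**k = 0.6.**
- Means 0.76 and 0.84; spurious deficit 1 − 0.76/0.84 = 9.5%.
- Variances 0.0246 + 0.0384 = 0.0630 (MRSE) and 0.0298 + 0.0384 = 0.0682 (non-MRSE); pooled SD 0.254; SE 0.0569.
- Non-centrality 0.08/0.0569 = 1.41; significant in 28.5% of trials.

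**k = 0.7.**
- Means 0.82 and 0.88; spurious deficit 1 − 0.82/0.88 = 6.8%.
- Pooled SD 0.225; SE 0.0504; non-centrality 0.06/0.0504 = 1.19; significant in 21.8% of trials.

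**Sensitivity (same method).**

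| Women, MRSE vs non-MRSE | k | Spurious deficit | Significant |
|---|---|---|---|
| equal (50% vs 50%) | any | 0% | 5% |
| 50% vs 40% | 0.6-0.7 | 3-5% | 9-10% |
| 60% vs 40% | 0.8 | 4% | 14% |
| 60% vs 40% | 0.6-0.7 | 7-10% | 22-29% |
| 65% vs 35% | 0.6-0.7 | 10-14% | 43-57% |

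These rates treat the percentages as those of the populations sampled. If exactly 36 of 60 and 12 of 30 enrolled patients are women, the deficit is the same, but simulation (40,000 runs) gives 16-19% significant for k = 0.6 to 0.7. A separate fixed-count simulation with 50% or 60% women against 30%, and k from 0.6 to 0.8, gave 11-57% unadjusted and about 5-6% after adjustment for sex. On within-patient percent change, assumed unrelated to sex, it gave about 5% throughout.

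**Precision when the groups are balanced (50% women in each).**
- Within-sex share of variance: 0.0272/0.0672 = 40% (k = 0.6); 0.0298/0.0523 = 57% (k = 0.7).
- Detectable difference at 80% power: (1.960 + 0.842) × 0.2236 = 0.63 SD.
- k = 0.6: 0.63 × 0.259/0.80 = 20% of the mean unadjusted; 0.63 × 0.165/0.80 = 13% adjusted.
- k = 0.7: 0.63 × 0.229/0.85 = 17% unadjusted; 0.63 × 0.173/0.85 = 13% adjusted.

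**The case against.** **The planned contrast is percent change, not Nm.** A reader might infer that the main MRSE against non-MRSE analysis is run on raw Nm. The protocol does not say so. Nm is a reporting unit. The primary efficacy parameter and the subgroup comparison by symptoms are on percent change, where each patient is their own control and stable differences in level largely cancel. This objection stands and limits the point to the on-statin level comparison. Percent change could be biased only if sex, age or weight alters the response to withdrawal or the retest effect.

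**The level comparison is implied rather than specified.** Primary outcome (2) could be read as recovery after withdrawal, and the ANOVA sentence is general. That is fair as far as it goes. But Hypothesis 1 is about state while on the drug, Hypothesis 2 covers withdrawal separately, and a case-control comparison is announced. Percent change alone cannot answer Hypothesis 1.

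**Covariates belong in a statistical analysis plan that is not shown.** They may be there. However, the pairing factors are fixed in this protocol, and section 5.0 does name a test, which is unadjusted. The point concerns what is written.

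**No imbalance is shown.** This stands. The splits used above are assumed. The protocol's preliminary MRSE series had 6 men and 3 women (33% women), which is too small to settle the matter but does not suggest a mostly female group. The listed risk factors follow a discussion of rhabdomyolysis, while this trial enrols patients with normal CK. The 30-60 age limit also narrows the part due to age.

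**Conclusion.** The point holds for one comparison: on-statin levels of strength and endurance in MRSE against non-MRSE patients. As written, that comparison is non-randomised, paired on statin and dose only, and has no stated protection against differences in sex, age or body weight.

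Under the stated assumptions, a 60% against 40% sex split gives a spurious deficit of about 7-10%, significant in about 22-29% of trials. With an equal mix there is no bias from sex, but the unadjusted test still carries roughly twice the variance it needs (adjusted share 40-57%). Age and body weight were not modelled. A purely relative fatigue measure would be affected less than torque or work.

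The documents do not support saying that the comparison *is* confounded, because that needs an actual imbalance. Nor do they support saying that the primary percent-change analysis is compromised. The change is worth making because it protects a named primary outcome at almost no cost.

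**What to change.** Add to section 5.0 wording along these lines: *On-statin (baseline) torque, work and handgrip strength will be compared between patients with and without MRSE using a linear model on log-transformed values, with group, sex, age and body weight as covariates. The pairing on statin and dose will be taken into account, with statin and dose grouped to avoid sparse cells. Results will be given as adjusted ratios with 95% confidence intervals.*

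Leave the 10 statin-naïve controls out of this model. Statin and dose are undefined for them, and the protocol includes them to assess test-retest variability. Keep percent change as the primary efficacy parameter.

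The cost is wording only. Body weight is already measured in all patients (4.0, Clinical and anthropometric measures), and age and sex are needed for eligibility and for the Objective #2 strata. No visit, measurement or participant is added.
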